#### Physical functions

For participants who are not wheelchair bound the following tests are used to assess physical functioning in multiple domains.

The Timed Up & Go test (TUG) is used to measure functional mobility [44]. The participant is instructed to rise from a chair, walk 3 m, make a turn, walk back and sit down in the chair, as fast as possible, but without running. Participants are allowed to use their hands while standing up and also walking devices are allowed during test performance. Two trials are performed and the average time is the outcome, lower scores implying better functional mobility.

The FICSIT-4 measures static balance [45]. Participants are asked to perform a stance with two feet parallel, semi tandem, tandem and on a single leg. The participant has to hold every stance for 10 s. If a stance cannot be held for 10 s, the test stops. Scores can range from 0 to 5, with higher scores indicating better performance.

A 6-m walking test is used to assess walking speed. Participants are instructed to walk 10 m as fast as possible, but without running. Time registration starts after 2 m and stops 2 m before the end of the 10 m track. The use of a walking aid is allowed. For each participant three attempts are timed, the mean time of three trials is used as score, a lower score implies a better performance.

#### Care burden

Care burden of both the primary informal caregiver as well as the primary formal caregiver is assessed with a set of brief questionnaires.

The Caregiver Strain Index (CSI) is filled in by the primary informal caregiver and evaluates (over)load of the family caregiver on 13 yes/no items [46].

The short version of the Zarit Burden Interview (ZBI) evaluates care burden of the primary informal caregiver [47]. It consists of 12 5-point Likert scale questions and is widely used in dementia caregiving research. Scores can range between 0 and 48. Higher scores represent higher care burden.

Next to the short standardized questionnaires, care burden of both the primary formal caregiver as well as the primary informal caregiver is evaluated with an adapted Borg scale (originally used in sports as a measure of perceived exertion). Scores can range between zero and fourteen, zero indicating no care burden at all and fourteen indicating maximum care burden.

#### Cost-effectiveness

To evaluate the cost-effectiveness of the passive exercise interventions, QOL outcomes and costs need to be determined. The outcomes of the EQ-5D-5 L will be used to calculate quality adjusted life years (QALYs). QALYs are expressed as a number between 0 and 1, where 0 indicates death and 1 indicates optimal QOL, multiplied with the life expectancy of the person. To estimate the costs of the intervention, the hours of intervention and the costs of the MSim platform will be included. Cost-effectiveness will be specified as the incremental cost-effectiveness ratio (ICER), which is defined by the cost per incremental QALY. Separate cost-effectiveness ratios will be calculated for each type of passive exercise, compared to regular care using the following formulae: ICER = (Costs Intervention – Costs Control)/(Effect Intervention – Effect Control).

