Although MSim is already being used in multiple health care settings, any effects of MSim alone or combined with WBV have not yet been established. The current study primarily aims to investigate the effects of the three different forms of passive exercise on QOL and ADLs of institutionalized patients with dementia. The secondary aims are to assess the effects of the three different forms of passive exercise on cognitive functioning and physical functioning of institutionalized patients with dementia as well as on care burden of both the primary formal and primary informal caregivers of these patients. Cost-effectiveness of the interventions will also be analyzed. It is hypothesized that MSim and WBV, due to their own specific working mechanisms, both will lead to an improvement in QOL, ADLs and cognitive functioning, but that the combination of MSim and WBV will lead to a stronger cognitive effect as a results of complementary working mechanisms. In addition, it is hypothesized that improvement in ADLs and improved cognition will lead to more independent and better daily functioning of the patient, causing a reduction in need for care and consequently lower the care burden of the primary formal and informal caregiver..

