### Study procedures

The participants of this study will be recruited via the medical staff of nursing homes. The medical staff and nurses, who are informed about the aim and procedure of the study, select potential participants within the different wards of the nursing homes. The potential participants and their legal representatives then receive an information letter with informed consent. The legal representatives of the potential participants can provide written informed consent, and in addition patients will have to orally agree to participate. After informed consent is given by the legal representatives, participants will be screened for eligibility.

Measurements for cognitive and physical function are administrated by trained research assistants who are blinded for group allocation. Questionnaires for QOL, ADLs and care burden are given or send to respectively the primary formal and primary informal caregiver. Tests and questionnaires for all outcome measures are assessed at baseline (T0), after the intervention period of six weeks (T1) and two weeks after the intervention has ended (T2). All test moments of a given participant are performed at the same time of the day and are assessed by the same research assistant. Also the questionnaires for both the primary formal and primary informal caregiver are filled in by the same person on each given time point. An overview of the enrollment and study design is given in Fig. 2.

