#### Interventions

All participants in the intervention groups receive the intervention four times a week for six consecutive weeks. During these six weeks, participants in the control group receive regular care.

The first intervention group receives MSim. During a session, three short, real life movies of approximately four minutes are shown of multiple activities (e.g. motor riding, dancing or horse riding) and from various perspectives. Matching music and sounds are played and the platform moves synchronically with the movies. This way, the participant on the platform moves in a passive way and is stimulated multisensory by means of visual, auditory, tactile and proprioceptive stimuli.

During WBV, the platform vibrates with a 30 Hz frequency and an amplitude of 1–2 mm. In an earlier study it was shown that these vibrations can safely be applied in old adults [28]. The duration of the WBV sessions is set to four minutes. During the WBV session a stationary motorcycle with idling engine is shown on the screen and matching sounds are played.

For the MSim + WBV intervention, the former two forms of passive exercise are combined. During 12 min participants alternately receive MSim (4 min) and WBV (2 min).

All forms of passive exercise will be applied using two commercially available motion simulation devices (the balancer, Fig. 1a and the wheelchair pod, Fig. 1b). During the sessions, participants are asked to take place on either one of the platforms and focus on the television screen. Hands are placed on the sidebars of the balancer or the wheelchair. Preferably the participant is seated as upright as possible.

The types of movies,the movement intensity of the platform and vibration intensity are documented. After each session the participant will be asked how much he/she enjoyed the session. Scores can be given on a scale ranging from zero to ten, with zero meaning they did not enjoy the session at all and ten meaning that they really enjoyed the session. Also, in the MSim and MSim + WBV group, the participants are asked which movies of the session they liked the most. For the MSim and MSim + WBV group respectively a top 3 or top 2 is documented. In the first week, at least one movie of each activity will be shown to the participant. After the first week, if any preferences are known for a participant, movies shown in the remaining sessions are chosen based on these preferences.

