### Outcome measures

#### QOL and ADLs

To assess QOL and ADLs a series of questionnaires are used.

The EQ-5D-5 L [29] is filled in by the primary formal caregiver. It consists of five 5-point Likert scale questions, and is used to measure health-related quality of life based on five different domains (mobility, self-care, usual activities, pain/discomfort, anxiety/depression). An index value can be computed using the Crosswalk Index Value Calculator [30] with the value set from the Netherlands; an index value closer to 1 resembles a better quality of life. This index value of the EQ-5D-5 L can also be used for cost effectiveness analyses.

The Qualidem [31] is also filled in by the primary formal caregiver. The questionnaire consists of 40 items on a 4-point Likert scale and is specifically developed to quantify QOL in institutionalized patients with dementia. The following subscales can be distinguished: care relationship, positive affect, negative affect, restless tense behavior, positive self-image, social relations, social isolation, feeling at home, having something to do and other. A sum score between 0 and 120 can be obtained, a higher score reflects a better quality of life.

The Older Persons and Informal Caregivers Survey Minimum DataSet (TOPICS-MDS) is a set of brief, standardized questionnaires filled in by the primary informal caregiver, if possible in consultation with the participant [32, 33]. Next to demographic characteristics, outcome measures are comorbidity, quality of life, mood, functional limitations, mental health, social functioning, care use and care burden. For QOL the TOPIC-MDS includes the EQ-3D-3 L and two questions adapted from the RAND-36 [34, 35]. For ADLs the TOPICS-MDS includes a modified version of the Katz Index and an additional indicator of mobility [36]. Respondents are asked if the participant requires assistance for six basic functions (e.g. dressing, eating and bathing), and seven instrumental functions (e.g. grooming and taking medication). Responses are rated on a binary scoring system (dependent = 1; independent = 0) and summated, with higher scores representing greater functional limitations [32].

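### QALYs are defined as utility times remaining life expectancy, so a difference observed over at most 8 weeks is carried to death without waning or matching costs

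*Protocol article*

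**What the plan says.** The Cost-effectiveness section of the protocol article gives one rule for QALYs. It names the source of the utility: "The outcomes of the EQ-5D-5 L will be used to calculate quality adjusted life years (QALYs"). It then defines the QALY as a 0-to-1 value, "where 0 indicates death and 1 indicates optimal QOL, multiplied with the life expectancy of the person". For costs it says that "the hours of intervention and the costs of the MSim platform will be included". A separate ICER is planned for each of the three forms of passive exercise against regular care: the cost difference divided by the effect difference.

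Under Study procedures, all outcome measures are taken "at baseline (T0), after the intervention period of six weeks (T1) and two weeks after the intervention has ended (T2"). Under Interventions: "All participants in the intervention groups receive the intervention four times a week for six consecutive weeks".

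The article gives no life expectancy, cost, QALY or ICER figure. It gives no rule for waning of the effect and no period over which the platform cost is spread.

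**The concern.** Multiplying a utility by remaining life expectancy assumes that the utility stays at that level until death. The trial observes utility for 8 weeks, 6 of them during treatment. The T2 visit, two weeks after treatment ends, shows whether an effect outlasts the programme, but the rule has no place for that answer. The Background describes dementia as progressive, which does not suit a constant lifelong gain after six weeks of sessions.

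The effect side therefore has a lifetime horizon, while the cost side has no stated horizon and includes no continued use or later care. Because life expectancy is taken for each person, it also brings into the denominator a quantity that varies between residents for reasons unrelated to treatment.

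What is at stake is the cost-effectiveness statement for devices that, according to the Discussion, are already in use in care with little or no evidence of cost-effectiveness.

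**Working it through.** The protocol has no figure to reproduce. The check compares its rule with the usual within-trial QALY at the same incremental cost.

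**Inputs from the protocol:** utility at weeks 0, 6 and 8; QALY = utility × life expectancy (LE); ICER = cost difference / QALY difference.

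**Assumptions, not in the protocol:** equal utility at baseline; a utility difference dU = 0.05 at T1 (it cancels from the ratios); LE of 0.5 to 3 years, the same in both arms; 52 weeks per year.

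**Within-trial QALY difference (trapezoid over weeks 0, 6 and 8)**
- Gain kept to T2: dU × (0.5 × 6 + 2)/52 = dU × 5/52 = 0.096 dU. With dU = 0.05 this is 0.0048.
- Gain gone by T2: dU × (0.5 × 6 + 0.5 × 2)/52 = dU × 4/52 = 0.077 dU, or 0.0038.
- Gain present in full for all 8 weeks (the comparison kindest to the protocol): dU × 8/52 = 0.154 dU, or 0.0077.

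**Protocol rule:** dU × LE. The ratio to the within-trial value is LE/0.096, LE/0.077 or LE/0.154, whatever dU and the cost are.

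| Assumed LE (years) | Protocol QALY difference, dU = 0.05 | Ratio, gain kept to T2 | Ratio, gain gone by T2 | Ratio, gain for all 8 weeks |
|---|---|---|---|---|
| 0.5 | 0.025 | 5.2 | 6.5 | 3.3 |
| 1 | 0.05 | 10 | 13 | 6.5 |
| 2 | 0.10 | 21 | 26 | 13 |
| 3 | 0.15 | 31 | 39 | 19.5 |

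The fourth column supposes that the T1 utility enters the rule; the article does not say which visit supplies it. If T2 were used and the gain had gone, the rule would give a difference of zero.

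**Effect on the ICER.** Per 1,000 currency units of incremental cost, with the gain kept to T2, the within-trial ICER is 1,000/0.0048, about 208,000 per QALY. Under the protocol's rule it is 1,000/0.05 = 20,000 at LE 1 year and 1,000/0.15 = 6,667 at LE 3 years.

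**Negative difference.** With dU = −0.05 and LE 3 years, the rule gives a loss of 0.15 QALY against 0.0048 within the trial. The arm looks worse under both methods, and much worse under the protocol's.

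**Imbalance in life expectancy.** With equal utility in both arms (0.5, assumed) and a chance difference in mean LE of 0.1 to 0.5 year, the rule gives 0.5 × 0.1 = 0.05 to 0.5 × 0.5 = 0.25 QALY, in either direction, with no treatment effect. The lower figure already equals what the rule credits to a gain of 0.05 at LE 1 year.

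**The case against.** **The sentence may be only a loose textbook definition of a QALY, with detail left to a fuller plan.** This is possible, but it is the only calculation rule given, and it feeds directly into the ICER. It is a rule stated in a form that does not suit the design, and not a detail left out.

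**The 8-week area is a floor and not the truth.** This stands. It credits nothing after week 8, even when the gain is still present at T2. The ratios compare two horizons; they do not measure error against a known value, and they rest on life expectancies that the protocol does not give. An order of magnitude holds from about 1 year upwards if the gain is kept to T2. On the kindest comparison the factor is 6.5 at 1 year and about 3 at half a year.

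**Stratification limits imbalance.** This also stands in part. Randomization is stratified for gender, MMSE score, age and nursing home, which should restrain differences in life expectancy between arms without removing them.

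Three stronger readings are tempting, and the protocol does not support them:
- *Every ICER comes out too favourable.* The direction holds only for an arm with a positive utility difference and higher cost.
- *A lifetime of benefit is set against six weeks of costs.* The sessions last six weeks, but the horizon of the platform cost is not stated. Charging the full purchase price would push the ICER up.
- *Leaving out care use flatters the interventions.* TOPICS-MDS covers "mental health, social functioning, care use and care burden", and the Background expects better functioning to end in "causing a reduction in need for care and consequently lower the care burden". If that hypothesis is right, leaving care use out makes the ICER less favourable. Including it is a choice of costing perspective, and the article gives neither a recall period nor unit costs. It is not a required change.

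**Conclusion.** The point holds for the stated QALY rule. As written, it extrapolates a utility difference seen over at most 8 weeks to the end of life, without waning and without costs on a matching horizon. For an arm with a utility gain and higher cost, the ICER is lower than the within-trial estimate by a factor of about LE/0.096 years if the gain persists to T2, or LE/0.077 years if the T1 gain is used and has gone by T2. The sizes depend on the assumed life expectancy, not on the assumed gain. For losses the rule magnifies harm, and imbalance in life expectancy can move the result either way.

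Severity is moderate. The Background lists cost-effectiveness as an additional analysis, outside the primary and secondary aims. The primary QOL and ADL analyses, the randomization and the sample size are untouched.

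**What to change.** Reword the Cost-effectiveness section:
- In the main analysis, define QALYs as the area under the EQ-5D-5L index curve over T0, T1 and T2 (8 weeks), with the difference between arms adjusted for baseline utility.
- Count costs over the same 8 weeks, with the platform cost apportioned to that period and the basis of the apportionment stated.
- Present any lifetime extrapolation only as a labelled scenario, with an explicit assumption on waning and with matching long-term costs.

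The cost is a rewritten paragraph and a little analysis work. The QALY part needs no new data, because EQ-5D-5L is already planned at all three visits. Apportioning the platform needs an assumption about its service life and use. The sponsor should expect small QALY differences (about 0.005 for the assumed gain of 0.05) and probably less favourable ICERs for any arm that shows a benefit.

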### Sample size calculation

Sample size is calculated with Sample Power 3. Since there is no data available on MSim or any comparable intervention, the sample size is calculated with an effect size estimation based on results of pilot studies on the chronic effects of WBV on cognition. Two pilot studies used the Stroop test score to evaluate these effects and resulted in an effect size of f = 0.22 [unpublished observations]. Power analyses with this value and use of repeated measures ANOVA, alpha 5%, power 80% and expected drop-out of 15% results in a minimal sample size of 49 participants per group.

Some additional remarks are needed to explain this sample size calculation. Since pilot data for QOL and ADLs are not available, the sample size estimation is based on the secondary outcome measure cognition and not on the primary outcome measures quality of life and daily functioning. Moreover, we are fully aware of the fact that with the calculated sample size additional subgroup analyses lack power. Including these analyses in the sample size calculation would result in unrealistic high sample sizes which would be practically impossible to realize due to factors like available budget, duration of the study and available number of potential participants. Additional analyses will be performed but will be considered exploratory.

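### The ICER is fixed as the cost-effectiveness result for three comparisons, on an EQ-5D denominator the trial was not sized for; incremental net benefit with an interval should carry the economic conclusion

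*Protocol article*

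**What the plan says.** The Cost-effectiveness section (Methods, Outcome measures) chooses the measure: "Cost-effectiveness will be specified as the incremental cost-effectiveness ratio (ICER), which is defined by the cost per incremental QALY". It gives the formula "ICER = (Costs Intervention – Costs Control)/(Effect Intervention – Effect Control" and adds: "Separate cost-effectiveness ratios will be calculated for each type of passive exercise, compared to regular care". That makes three ratios.

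For the denominator, "The outcomes of the EQ-5D-5 L will be used to calculate quality adjusted life years (QALYs", with the utility value "multiplied with the life expectancy of the person". For the numerator, "the hours of intervention and the costs of the MSim platform will be included". No other cost component is named.

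The Sample size calculation section rests on an effect of f = 0.22 from pilot data on the Stroop test. It says that quality of life could not be used because there were no pilot data for it. The "expected drop-out of 15% results in a minimal sample size of 49 participants per group".

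**The concern.** A ratio of differences is well behaved only when its denominator is clearly away from zero. If the interval for the QALY difference includes zero, the corresponding interval for the ratio is unbounded. A small movement of the QALY difference across zero then turns a very large positive ICER into a very large negative one, although the evidence has hardly changed. Nothing in the trial's sizing protects the denominator.

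Negative ratios also carry no order. If the plan is followed as written, chance can largely decide whether a programme is reported with a favourable, an enormous or a negative cost per QALY. That would remain so even if costs and utilities were measured perfectly.

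**Working it through.** **Number evaluable.** The plan's own figure is 49 per group including 15% drop-out: 49 × 0.85 = 41.65, so 41 to 42 evaluable. In the other direction, 41 / 0.85 = 48.2, which rounds up to 49. A between-group repeated-measures test at f = 0.22, alpha 5% and power 80% needs 41 per group with two measurements at a within-person correlation of 0.40 to 0.42, or with three at 0.54 to 0.56. The article states neither the correlation nor the number of measurements, so 49 is attainable but cannot be verified. It matters here only through the number evaluable.

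**Precision of the denominator.** In standard-deviation units with n = 41 per arm, SE = √(2/41) = 0.221. The 95% half-width is 1.96 × 0.221 = 0.43 SD, and the difference detectable with 80% power is 0.62 SD.

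**Behaviour by true effect.** With z = d / 0.221:
- P(95% interval includes zero) = Φ(1.96 − z) − Φ(−1.96 − z)
- P(wrong sign) = Φ(−z)

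| True d | z | Interval includes zero | Wrong sign |
|---|---|---|---|
| 0.2 | 0.91 | 85% | 18% |
| 0.44 | 1.99 | 49% | 2% |
| 0.5 | 2.26 | 38% | 1% |
| 0.8 | 3.62 | 5% | about 0% |

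The values 0.2, 0.5 and 0.8 are the benchmarks in the Statistics section. The value 0.44 is f = 0.22 read as a two-group effect (2 × 0.22). With 42 per arm the first three interval figures are 85%, 48% and 37%.

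**Three ratios with a shared control.** By simulation with equal true effects in the three arms, at least one of the three denominators has an interval including zero in about 97% of trials at d = 0.2, 74% at d = 0.44 and 63% at d = 0.5.

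**Cross-check on the utility scale (assumed inputs).** Take an index SD of 0.20 to 0.30, a baseline correlation of 0 to 0.7 and 42 per arm. Then SE = SD × √(1 − ρ²) × √(2/42) = 0.031 to 0.066. At a true gain of 0.05 the interval includes zero in 64% to 88% of trials. This covers small effects only: 0.05 / 0.30 = 0.17 to 0.05 / 0.20 = 0.25 SD before baseline adjustment.

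**Life expectancy.** A multiplier common to everyone cancels from these probabilities. A multiplier that differs between persons does not. Assume life expectancy with mean 3 years and SD 1.5 years, baseline utility 0.5, utility SD 0.20 and d = 0.2. The ratio of the mean difference to its standard error then falls from 0.91 to 0.53, and the wrong-sign chance rises from 18% to about 29%.

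**Negative ratios have no order.** Three invented arms, each dearer and worse than control:
- A: +500 and −0.01 QALY gives −50,000.
- B: +1,000 and −0.02 QALY gives −50,000, the same ratio, yet B is worse on both counts.
- C: +500 and −0.02 QALY gives −25,000, nearer zero than A, yet C costs the same and loses more.

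Net benefit at a threshold of 50,000 is −500 − 500 = −1,000 for A, −1,000 − 1,000 = −2,000 for B and −1,000 − 500 = −1,500 for C, which is the right order.

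**Ratio against net benefit (assumed inputs).** Take utility SD 0.20, an 8-week horizon, 41 per arm and extra cost 500 per person (SD 200). At d = 0.2 the true ICER is 500 / (0.04 × 8/52) = 81,250. Its central 95% sampling range is about −744,000 to +803,000, with 18% of ratios negative. Net benefit at 50,000 averages −193, with a range of −863 to 478. At d = 0.44 the ICER range is about 14,100 to 220,200, and net benefit runs from −494 to 849.

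**The case against.** The ICER is a conventional measure and is correctly defined as a ratio. A condensed article may leave intervals, bootstrap, thresholds and acceptability curves to a fuller document, so their absence is no finding. That stands, and the point does not rest on it. It rests on the positive choice of the ratio as the result; adding an interval elsewhere would not help in trials where that interval is unbounded.

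A reader might infer that a negative ICER here has two opposite readings, dearer and worse or cheaper and better. The article does not support this. The only costs it names are intervention hours and the platform. Regular care incurs neither, so the numerator is positive and a negative ratio means dearer and worse. The Background does hypothesise benefits "causing a reduction in need for care and consequently lower the care burden of the primary formal and informal caregiver", and TOPICS-MDS records care use, but nothing in the Cost-effectiveness section puts care use into the costs. The second reading arises only if other care costs are added.

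A reader might also infer that the trial cannot tell the QALY difference from zero. That goes too far. At d = 0.8 the interval includes zero in only about 5% of trials. At contrasts compatible with f = 0.22 (d = 0.44 to 0.62) the figure is about 49% down to 20%. Since f = 0.22 is a cognitive effect, it does not settle the EQ-5D effect either way.

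Finally, cost-effectiveness is not among the primary or secondary aims; the Background adds that it will also be analysed. This limits the weight of the point but does not remove it.

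**Conclusion.** The concern holds in a limited form. The article makes an ICER the cost-effectiveness result for each of three comparisons, on a denominator that played no part in the sample size. For small to moderate effects the ratio is often unstable, with an unbounded interval in about 85% of trials at d = 0.2, 49% at d = 0.44 and 38% at d = 0.5. For large effects the problem largely disappears. Negative ratios cannot be ranked at any effect size, and person-specific life expectancies can add further noise.

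These figures assume 41 evaluable per arm, a normal approximation and no baseline adjustment beyond what is already in d. The true EQ-5D effect and SD are not in the article. The change is worth making, but the point does not touch the primary outcomes.

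**What to change.** For each comparison with regular care, report incremental net benefit = threshold × QALY difference − cost difference, over a stated range of thresholds. Give 95% intervals from a bootstrap that resamples each participant's cost and QALY together within arm, and base the economic conclusion on this result. Keep the ICER as a secondary description, quoted only when both the cost and the QALY difference are positive.

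The cost is about one paragraph of the plan and a little more analysis on data already being collected. Thresholds must be chosen and stated in advance. The economic result will look less decisive: in both illustrations above, net benefit at 50,000 still spans zero, because it displays the imprecision and does not remove it.

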#### Randomization

After baseline measurements and stratification for gender, MMSE score, age and nursing home, participants are randomly assigned (1:1:1:1 allocation ratio) to one of the four groups (MSim, WBV, MSim + WBV or regular care which serves as the control condition) by using random numbers. The randomization procedure is performed by a blinded scientist who is not related to the study.

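### Cost-effectiveness ratios are planned only against regular care, so they cannot show which of the three programmes is the best value

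*Protocol article*

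**What the plan says.** The trial has three active programmes and a control: "participants are randomly assigned (1:1:1:1 allocation ratio) to one of the four groups" (Randomization). For the economic analysis, the Cost-effectiveness section says: "Separate cost-effectiveness ratios will be calculated for each type of passive exercise, compared to regular care". The formula that follows divides the cost difference between intervention and control by the effect difference between intervention and control, so the control arm is the reference every time.

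On the cost side: "To estimate the costs of the intervention, the hours of intervention and the costs of the MSim platform will be included". The effect is the QALY, derived from the EQ-5D-5L.

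The Interventions section puts all three programmes on the same two devices, four times a week for six weeks. It says of WBV: "The duration of the WBV sessions is set to four minutes". An MSim session shows three films of roughly four minutes each, and an MSim + WBV session lasts 12 minutes.

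No section plans a ratio between programmes, an ordering by cost or a check for dominance. The Discussion remarks that the interventions can be compared with one another, but in a paragraph about which component caused an effect. The pairwise tests in the Statistics section concern outcomes, not value for money.

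**The concern.** A home that owns the platform chooses among four mutually exclusive strategies for a resident: no programme, WBV, MSim, or MSim + WBV. For that choice the relevant ratio sets the extra cost of a programme against its extra effect over the next cheaper option still worth considering. A ratio against regular care averages the good value of the first, cheaper minutes with the possibly poor value of the later ones. It can therefore look acceptable when the additional minutes buy almost nothing.

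The article says that these interventions are already in use with little evidence of cost-effectiveness, so readers are likely to compare the three ratios. Intervention hours are a named cost and differ between programmes. The stated hypotheses also allow small differences in QALYs: the combination is expected to be stronger on cognition, whereas the EQ-5D-5L domains listed under Outcome measures contain no cognition item.

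**Working it through.** The article prints no cost, QALY gain, ratio or threshold, so there is no figure to reproduce. Only the platform time follows from the text.

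**Step 1: platform time per participant (Interventions section).** Sessions: 4 per week x 6 weeks = 24.

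- WBV: 24 x 4 min = 96 min = 1.6 h
- MSim: 24 x (3 x about 4 min) = about 288 min = 4.8 h
- MSim + WBV: 24 x 12 min = 288 min = 4.8 h

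The contrast is threefold between WBV and the other two. MSim and MSim + WBV are about equal.

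**Step 2: why the two ratios can differ.** Let C and E be the extra cost and QALYs over regular care, with subscript w for WBV and c for a 12-minute programme. Then

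C_c/E_c = (E_w/E_c) x (C_w/E_w) + ((E_c - E_w)/E_c) x step, where step = (C_c - C_w)/(E_c - E_w).

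So the ratio against care is a weighted average of the WBV ratio and the step. The step is the larger whenever E_c/E_w is below C_c/C_w. If cost is hours alone, that means whenever the longer programme gains less than 288/96 = 3 times what WBV gains.

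**Step 3: illustration (assumed: 1 cost unit per minute, no other cost difference from regular care).**

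| Gains (WBV; 12-min) | WBV vs care | 12-min vs care | Step over WBV |
|---|---|---|---|
| 0.010; 0.012 | 96/0.010 = 9,600 | 288/0.012 = 24,000 | 192/0.002 = 96,000 |
| 0.010; 0.020 | 96/0.010 = 9,600 | 288/0.020 = 14,400 | 192/0.010 = 19,200 |

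Check of row 1 by Step 2: (0.010/0.012) x 9,600 + (0.002/0.012) x 96,000 = 8,000 + 16,000 = 24,000.

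**Step 4: range (assumed hourly cost and gains).** At 50 per hour the costs are 1.6 x 50 = 80 and 4.8 x 50 = 240.

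| Cost per hour | Gains | WBV vs care | MSim + WBV vs care | Step |
|---|---|---|---|---|
| 50 | 0.030; 0.031 | 2,667 | 7,742 | 160/0.001 = 160,000 |
| 100 | 0.030; 0.031 | 5,333 | 15,484 | 320,000 |
| 150 | 0.030; 0.031 | 8,000 | 23,226 | 480,000 |
| 50 | 0.020; 0.021 | 4,000 | 11,429 | 160,000 |
| 100 | 0.020; 0.021 | 8,000 | 22,857 | 320,000 |
| 150 | 0.020; 0.021 | 12,000 | 34,286 | 480,000 |
| 50 | 0.010; 0.030 | 8,000 | 8,000 | 160/0.020 = 8,000 |

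At an assumed threshold of 50,000 or 80,000, the first six rows all put MSim + WBV under the threshold against care and over it against WBV. At 20,000, three of the six do. In the last row the gains are in the ratio 3 to 1 and nothing is distorted.

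**Step 5: platform cost.** Suppose an equal 500 per participant is added to the Step 3 costs. With gains of 0.010 and 0.012, the ratios against care become (96 + 500)/0.010 = 59,600 and (288 + 500)/0.012 = 65,667, and the step stays at 96,000. With gains of 0.010 and 0.020, the longer programme costs 788/0.020 = 39,400 against care and its step is still 19,200. WBV, at 59,600, is then extendedly dominated. Which programme is the poorer buy thus depends on inputs that the article does not give.

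**The case against.** The trial is framed as three programmes, each against regular care. For that question the planned ratio is the correct one, and this stands. The article states no willingness-to-pay threshold and does not say that it will recommend one programme over another. It also stands that the ratios share a comparator: if mean cost and mean QALYs are reported by arm, a reader can obtain every increment by subtraction. The loss is one of analysis and interpretation, not of data. The article does not, however, commit to such reporting.

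The size of the distortion is conditional. It rests wholly on assumed costs and gains. The article also describes QALYs as a utility multiplied by life expectancy, so the scale of the gains is unknown. The 3 to 1 ratio counts platform minutes; set-up or transfer time, if counted as intervention hours, would shrink it. MSim and MSim + WBV need about the same time, so with equal platform cost their ratios against care already rank them by effect.

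A condensed article may leave net benefit and uncertainty methods to a fuller plan, so their absence is no fault. The comparator is different, because the article fixes it, with a formula.

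A reader might go further and infer that the economic conclusion would be wrong even with perfect data. The documents do not support that: the programme-versus-care answer remains valid, and for some inputs all the ratios agree. A reader might also infer that costs are wrongly confined to the intervention, since less need for care is hypothesised and TOPICS-MDS lists care use. That is not supported either. The text says what enters the intervention cost without excluding other costs, and it keeps a separate control-cost term. TOPICS-MDS is completed by the informal caregiver, and its items are not shown to be usable for costing ward care.

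**Conclusion.** The point holds in limited form. As planned, the ratios can say whether each programme is worth adding to regular care, but not which of the three is the best value. That the analysis stops there is inferred from the stated comparator and from the absence of any between-programme cost comparison.

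The threefold difference in platform time between WBV and the 12-minute programmes follows from the schedule. Everything beyond that is assumption: depending on the gains, the step over WBV may be four times the ratio against care (96,000/24,000), about a third higher (19,200/14,400) or equal to it. The analysis is neither a primary nor a listed secondary aim, so this is an improvement worth making rather than a flaw in the trial's main inference.

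**What to change.** Keep the three ratios against regular care and add a full incremental analysis to the Cost-effectiveness section:

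1. Report mean cost and mean QALYs for each of the four arms.
2. Order the four strategies by mean cost.
3. Remove any that is dominated (costs at least as much as another with no greater effect) or extendedly dominated (has a higher ratio than the next more effective option).
4. Report each remaining strategy's ratio against the next cheaper one, or compare net monetary benefit across the four arms over a range of thresholds.

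This uses the cost and EQ-5D-5L data already planned and changes neither design nor data collection. It costs a few sentences and a little computation. The downside is that some programmes may look less favourable than they do against regular care alone.
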